## Method

### Design

A cluster-randomized trial was designed as diagrammed in Fig. 1. Hospitals were the unit of randomization and twelve similar county-level hospitals were allocated one-to-one to the intervention and control arms of the study. The efficacy of the intervention was determined by comparison to the current standard of care (SOC, control arm) at 30 days, 90 days, and 12 months.

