### Sample size

A minimum sample size of 180 participants per arm, across 12 clusters (or 30 participants per cluster) was selected. This sample size was expected to achieve 93% power based on a one-sided test (at alpha = 0.05) to detect a difference between the group proportions of 0.28, where under the alternative hypothesis the One4All arm proportion was assumed to be 0.50 and the control arm proportion was assumed to be 0.22. This calculation assumed an intra-class correlation (ICC) within hospitals of 0.082 based on preliminary data. Although 30 participants per cluster (or hospital) was the target, it was expected that some hospitals would enroll participants more quickly than others. Therefore, a final study population of greater than 180 participants per arm was anticipated as enrollment at all hospitals remained open until the last hospital met its 30-participant goal.

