### Outcomes

The primary outcome measure was the proportion of participants who achieved testing completeness and received test results and post-test counseling within 30 days of positive screening. Testing completeness was defined as completion of three required components: 1) initial HIV screening (one to two tests in One4All and two to four in SOC), 2) CD4 testing, and 3) confirmatory HIV testing—WB in the SOC arm, or VL in the One4All arm. “Success” was defined as completion of all three required tests and notification of test result along with receipt of counseling after each test. Success was compared at 30 days after initial HIV-positive screening. The secondary outcome measure was the proportion of participants who initiated ART within 90 days from the date of HIV-positive screening. ART-initiation was defined as the receipt of the first ART prescription. Tertiary outcomes included the proportion of participants who achieved viral suppression (≤200 copies/mm^3^) and mortality at 12 months. Mortality was assessed as the number of reported deaths divided by the number of patients enrolled.

Aside from these main outcome measures, three other measures were pre-specified. For the primary outcome, two further analyses were planned: time from initial positive HIV screen to success, not restricted to the 30-day window, compared between control and intervention arms, and success at 45, 60, and 90 days, also compared between control and intervention arms. For the secondary outcome, one further analysis was planned: time from initial positive HIV screen to ART initiation, not restricted to the 90-day window, compared between control and intervention arms.

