Analytical methods and the adjustment for clustering and covariates effects used in the analysis of the primary outcome were also applied to the ART initiation secondary outcome and viral suppression tertiary outcome. As with the secondary analysis of the primary outcome, Kaplan-Meier analyses were also performed for time to initiation of ART, outside the 90-day window, and time to death. In addition, for the mortality outcome, a random effects Cox (shared frailty) model accounting for the hospital clustering effect was used to calculate the intervention effect on the hazard ratio (HR) of death while also controlling for other covariates. Adjustments to *p*-values and confidence intervals for multiple testing and multiple comparisons were not performed. All data analyses were performed using SAS software (SAS Institute, Inc., USA).

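### Mortality inference rests on one shared-frailty Cox model with 12 hospitals; if the usual large-sample test is used, its error rate is likely to be moderately inflated, and a within-stratum permutation p-value would prevent this

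*Protocol article*

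**What the plan says.** The Design section sets the number of independent units: "Hospitals were the unit of randomization and twelve similar county-level hospitals were allocated one-to-one". Allocation and blinding adds that randomisation was stratified: eight hospitals with low historical testing completion were split 4:4, and four with high completion were split 2:2.

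The Data analysis section carries the primary-outcome methods (a random-effects model plus a cluster-adjusted chi-square check) over to ART initiation and viral suppression. Mortality is not in that sentence. For deaths the article gives three things:

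- a crude proportion, in Outcomes: "Mortality was assessed as the number of reported deaths divided by the number of patients enrolled";
- a descriptive display with no test named: "Kaplan-Meier analyses were also performed for time to initiation of ART, outside the 90-day window, and time to death";
- the frailty model: "a random effects Cox (shared frailty) model accounting for the hospital clustering effect was used to calculate the intervention effect", with the effect expressed "on the hazard ratio (HR) of death while also controlling for other covariates".

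The article does not state how the frailty variance is estimated, which reference distribution is used, or which covariates enter this model. The same section does use permutation of treatments over hospitals, but only for baseline variables with more than two categories.

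**The concern.** The treatment effect is a between-hospital contrast, so its precision depends on how well 12 hospitals reveal the between-hospital variance. Two things can make the standard large-sample test too liberal. A normal reference ignores that the variance is estimated on about 10 degrees of freedom (9 with one hospital-level covariate). Maximum-likelihood-type estimation also tends to put that variance too low.

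The other three outcomes have a second, cluster-adjusted test as a consistency check. Mortality has none. It is one of the four outcomes named in the objective and the Conclusion, no multiplicity adjustment is made, and the Discussion hopes that the results will support replacing the current care cascade. An interval for the hazard ratio that is too narrow would make a chance difference in deaths look firmer than it is.

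**Working it through.** **Inputs from the article.** 12 hospitals, 6:6 (Design); strata of 8 and 4 hospitals, split evenly (Allocation and blinding); "A minimum sample size of 180 participants per arm, across 12 clusters (or 30 participants per cluster) was selected" (Sample size). The same section expects some hospitals to exceed 30, because enrolment stays open until the slowest reaches its target.

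**The article's own figure.** The only stated operating characteristic is 93% power for the primary outcome (0.50 v 0.22, one-sided 0.05, ICC 0.082). Design effect = 1 + (30 - 1) x 0.082 = 3.378. Effective n per arm = 180 / 3.378 = 53.3. One-sided power is 92.3% (pooled variance) or 93.4% (unpooled), so the figure reproduces. It says nothing about mortality, and 0.082 is the ICC for testing completeness, not for death.

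**Analytic approximation (two-sided 5%, critical value 1.96).**

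- Unbiased between-hospital variance: size = P(|t| > 1.96) = 7.8% with 10 df, 8.2% with 9 df.
- Variance too small by the factor df/12, as under ML: size = P(|t| > 1.96 x sqrt(df/12)) = 10.4% with 10 df, 12.4% with 9 df.

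These figures apply when between-hospital variation dominates. When it is small, the inflation shrinks or disappears, so simulation is needed.

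**Simulated size of the nominal 5% two-sided Wald test, no true effect, 12 hospitals.** All death rates and frailty variances are assumed.

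| Model fitted | Assumptions | Hospital sizes | REML-type | ML-type |
|---|---|---|---|---|
| Frailty Cox, penalised partial likelihood, 2000 trials per setting | deaths 10, 20, 30%; log-frailty variance 0 to 0.8 | 30 each | 3.8-7.8% | 4.1-10.5% |
| Frailty Cox, penalised partial likelihood, 600 trials per setting | deaths 20-30%; frailty SD 0.2-0.5 | equal | about 2-8% | about 5-13% |
| As above | as above | uneven | about 6-10% | about 6-13% |
| Exponential survival with lognormal frailty, 2000 trials per setting | deaths 20 or 30%; frailty SD 0.3 or 0.5 | 30 each | not run | 7.8-9.9% (no stratum covariate), 8.4-12.2% (with) |
| As above | as above | uneven, 30 to 110 | not run | 10.0-12.8% (no stratum covariate), 10.9-13.6% (with) |

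Monte Carlo standard error near 5% is sqrt(0.05 x 0.95 / 2000) = 0.5 points for 2000 trials and sqrt(0.05 x 0.95 / 600) = 0.9 points for 600.

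Within the first row, an approximate ICC for death of 0 to 0.02 gives 3.8-5.7% (REML-type) and 4.1-7.0% (ML-type). At about 0.08 the REML-type size is 6.8-7.8%. The ML-type size there is 8.1-8.6% without a hospital-level covariate and 10.0-10.5% with one. The last two rows fit a fully parametric model, not the Cox model that the article names, so they support the direction more than the exact size.

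**Alternatives.** In the first row's settings, a t reference with 10 or 9 df gives 1.7-4.6% (REML-type) and 1.9-6.7% (ML-type). In the uneven parametric settings it still gives 6.4-9.8%. It therefore over-corrects when hospitals differ little and can under-correct when sizes differ.

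Permutation within strata has C(8,4) x C(4,2) = 70 x 6 = 420 allocations. Each allocation has a mirror image, so the smallest two-sided p-value is 2/420 = 0.005, which is fine enough for a 5% test.

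**The case against.** The strongest reply is that this is silence in a condensed article. The text does not say that a Wald test with a normal reference is used, and the full protocol or an analysis plan, neither of which is at hand, may set the estimator and degrees of freedom. That stands: the missing detail is not itself an error, and the inflation is conditional on the usual test being used. What remains is a choice that the article does state, namely that deaths rest on a single random-effects model with 12 hospitals and no second cluster-level test.

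A reader might infer that the error rate is about twice nominal. The documents do not support that as a general statement. It needs a death rate, a between-hospital variance and an estimator that they do not give, and it appears mainly in the ML-type settings with larger hospital variation. The Setting section says that hospitals were chosen for homogeneity, so the inflation may be negligible.

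A reader might also infer that the investigators expect a significant mortality result. The Discussion suspects differences in several outcomes without naming mortality, and says that only the primary outcome is adequately powered. Limited power and tertiary status lower the stakes, but neither controls false positives.

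Finally, a correction is not free. A t reference can be conservative, for an outcome already short of power. That is a fair reason to prefer permutation over a blanket t correction.

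**Conclusion.** The point holds in a moderate, conditional form. The frailty Cox model is the only inferential method named for mortality, and it rests on six hospitals per arm. If its large-sample Wald test is used, the two-sided 5% error rate is likely to lie between nominal and about 8% with REML-type variance and equal hospitals. With uneven hospital sizes it reaches up to about 9-10%. About 10-13% arises only with ML-type variance and larger between-hospital variation.

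These ranges rest on assumed death rates of 10-30%, assumed frailty variances, an assumed estimator and an assumed normal reference. Neither the model nor the hazard ratio is wrong. The p-value and interval are what need protection.

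**What to change.** Keep the shared-frailty Cox model and report its hazard ratio. Take the p-value from re-fitting the model over all 420 reassignments of hospitals within the two randomisation strata, with covariates held fixed. This is valid whichever variance estimator the software uses, and it extends the hospital permutation already described for the baseline table. If an interval on the same basis is wanted, invert the test over a grid of hazard ratios. State the estimator and the sidedness of the test alongside.

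A t reference with 9-10 degrees of freedom can be reported as a simple sensitivity analysis (about 14% wider at 10 df: 2.228 / 1.960 = 1.137), noting that it may be conservative if hospitals differ little.

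The cost is a little programming, no new data, and a somewhat less favourable p-value or interval for a tertiary outcome.

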### Dissemination

The trial is registered with ClinicalTrials.gov (#NCT02084316) and the original protocol has been published on CTNDisseminationLibrary.org. The dataset is available upon request to the corresponding author.

## Discussion

To our knowledge this is the first controlled clinical trial to examine a bundle of interventions intended to improve multiple points in China’s HIV care cascade. A notable strength of this study lies in the rigor with which the effectiveness of the One4All strategy was tested. We expected that it would provide strong evidence in support of a streamlined HIV care cascade that accelerates diagnosis, complete clinical assessment, and treatment initiation having a significant clinical benefit over the current SOC.

With growing global evidence of the clear benefits of immediate ART for all PLHIV, both for the purposes of treatment of HIV infection and of prevention of HIV transmission [7, 8, 10], HIV/AIDS programs around the world must place renewed focus on optimization of the HIV care cascade. Worldwide, three out of every five PLHIV have not accessed ART [22]. Steps must be taken to eliminate losses to follow-up in the pre-ART period, and to ensure that all PLHIV receive immediate treatment.

At the time the present study was conducted, China still had a CD4 count ≤350 cells/mm^3^ ART eligibility criterion in place, with exceptions allowed only for PLHIV who were pregnant or in serodiscordant relationships [23] Thus, we expected that some participants in our study could not initiate ART despite being successfully retained in the pre-ART HIV care cascade. The WHO has since elevated the CD4 count threshold for ART to CD4 count ≤500 cells/mm^3^ in 2013 [24], and then abolished it in 2015, now recommending that all PLHIV receive immediate ART regardless of CD4 count [9]. Two studies in China have recently examined the benefit of ART initiation for PLHIV who did not meet the ≤350 cells/mm^3^ threshold. One prospectively examined immediate ART for all participants regardless of CD4 count [2], the other retrospectively investigated ART given to PLHIV with CD4 counts >500 cells/mm^3^ on an exception basis or as a part of the NCAIDS-sponsored “Prevention and Treatment of Major Infectious Diseases” project launched in 2012, which consisted of a series of cluster-randomized controlled trials among key populations. Both studies found significant improvements in mortality. We envision the combination of this evidence with the outcome of the present study supporting the complete replacement of China’s current SOC HIV care cascade with a new, streamlined cascade that accelerates diagnosis, complete clinical assessment, and ART initiation for all PLHIV.

Several important challenges were anticipated prior to trial commencement. For example, there was known variability in HIV SOC offered between different counties in Guangxi. A major cause of poor testing completeness and treatment initiation in rural Guangxi is disjointed HIV services as a result of structural and cultural constraints. County hospitals and CDCs struggle to follow national guidelines, mainly because of limited laboratory capacity and complex referral systems between hospitals and CDCs. The study team debated whether to provide strict guidelines and training to control arm study hospitals in an effort to standardize their current practice and improve homogeneity. However, we ultimately decided against tampering with the control condition, as we determined that a control comparator that represented the reality of the current standard HIV care cascade was more valuable than an artificial ideal control environment we would have created only for the benefit of the study. Therefore, during our baseline hospital investigations, the investigators engaged with hospital leaders and key personnel involved in HIV care and collected the key characteristics of the routine practice adopted at each county. A detailed testing to treatment flowchart was developed for each of the hospitals, documenting the key deviations from national guidelines. Then, CRFs were adjusted in order to accurately reflect the reality of testing and linkage to care procedures in each hospital.

Another key challenge was in the size of the study. The study was originally designed to include 24 hospitals (or clusters), 12 each in the control and intervention arms. This would have provided adequate power to detect differences between arms in all four outcomes. However, due to both the known high degree of variability observed in SOC services across counties in Guangxi and historically low numbers of patients screening HIV positive in many hospitals, not to mention the inherent difficulties with implementing such a large study, we decided to scale back the number of hospitals to 12. Although we suspected that we would still find statistically significant differences in several of the outcomes, the study was truly only adequately powered to detect between-arm differences in the primary outcome of testing completeness by 30 days.

As the study included no intervention related to ART regimen adherence, we anticipated the possibility that we may find no between-arm differences in achievement of viral suppression. We chose to define viral suppression as ≤200 copies/mL based on the equipment used for the study in local laboratories, recognizing that this target was aggressive. Although above the <50 copies/mL definition of viral suppression commonly recognized in high-income settings, it is well below the <1,000 copies/mL threshold recognized by the WHO as achievement of viral suppression in low- and middle-income countries such as China. It is also below the 300 to 500 copies per/mL target commonly used by research teams in studies in low- and middle-income settings [1, 25]. Future studies will need to examine interventions aimed at improving adherence in order to promote achievement of viral suppression. Additionally, with increased numbers of PLHIV on ART, it will be necessary for China’s public health and healthcare communities to be vigilant in monitoring patients for treatment failure. This will require substantial improvement of VL testing infrastructure and China should strongly consider investment in the development and implementation of new POC VL testing technologies, which further contribute to a streamlined HIV care cascade.

## Conclusion

This first-ever, cluster-randomized controlled trial of a bundle of interventions intended to streamline the HIV care cascade in China (the One4All strategy) was evaluated on four outcomes: testing completeness within 30 days, ART initiation within 90 days, viral suppression at 12 months, and all-cause mortality at 12 months. We expect that the outcome of this trial will provide strong evidence for the benefit of accelerating diagnosis, thorough clinical assessment, and ART initiation via an optimized HIV care cascade such as the One4All strategy. Furthermore, we anticipate that this evidence taken together with the strong, new evidence of both treatment and prevention benefits of immediate ART for all PLHIV regardless of CD4 count [7, 8, 10], will compel careful consideration by policymakers in China and other, similar low- and middle-income countries. HIV care cascade optimization is a critical strategy for meeting the UNAIDS 90-90-90 targets [26], and will be required for the eventual eradication of the HIV epidemic.

## Abbreviations

AIDS: Acquired immunodeficiency syndromes
ART: Antiretroviral therapy
CDC: Center for disease control and prevention
CRF: Case reporting form
CRIMS: Comprehensive response information management system
DST: Data and statistics team
EIA: Enzyme immunoassay
HIV: Human immunodeficiency virus
HR: Hazard ratio
ICC: Intra-class correlation
IRB: Institutional review boards
NCAIDS: National Center for AIDS/STD Control and Prevention
NIDA: National Institute on Drug Abuse
NIH: National Institutes of Health
One4All: The one-stop strategy intervention
PLHIV: People living with HIV
POC: Point-of-care
SOC: Standard-of-care
UCLA: University of California, Los Angeles
UNAIDS: The Joint United Nations Programme on HIV/AIDS
VL: Viral load
WHO: World Health Organization
